## 3. Expected Results and Discussion

### 3.1. Scientific and Public Health Significance

Sierra Leone continues to bear a disproportionate share of the global burden of maternal and neonatal mortality. Over a period of three years, we anticipate that this bundle will address the “second delay”—the delay in identifying and treating complications—by equipping facilities with the capacity to recognize and treat respiratory distress and hemorrhage immediately. By validating a bundle that includes both the Vayu bCPAP system and POCUS, we anticipate that this review will contribute to the global evidence base for low-cost, non-invasive respiratory support and maternal risk reduction in LMICs.

### 3.2. The Innovations

Two key innovations of this bundle are the expansion of bCPAP therapy and maternity unit point-of-care ultrasound coverage. Effective oxygen delivery requires blending and CPAP to avoid hyperoxic injury, a capacity which is often lacking in resource-constrained hospitals. Furthermore, the introduction of handheld ultrasound (Butterfly iQ3) into the delivery ward represents a task-shifting approach that we anticipate will empower midwives to perform advanced risk assessments at the bedside.

This bundle contains key clinical tools and practices with demonstrated effectiveness in other low-and-middle-income (LMIC) contexts. The Safer Birth Bundle of Care program in Tanzania achieved significant reductions in perinatal mortality through the deployment of similar scaling, service delivery improvements, and sustainability approaches using similar clinical tools. In a separate study from Tanzania, Vayu bCPAP implementation was associated with immediate improvements in respiratory function.

### 3.3. Comprehensive “Bundle” Approach

In contrast to single-intervention clinical studies, this protocol evaluates the implementation of a comprehensive service delivery bundle. We posit that improving newborn survival is impossible without simultaneously addressing maternal complications. By combining the WHO ENCC with maternal risk assessment and the WHO PPH Package, the implementation addresses the dyad of mother and baby, ensuring that survival for one is not compromised by the death of the other.

### 3.4. Supportive Supervision and Checklists

Evidence suggests that classroom training alone is insufficient to change clinical practice. Supportive supervision, defined as a collaborative, mentorship-driven process, rather than traditional inspection, has been shown to significantly improve health worker performance and motivation in low-resource settings [28,29,30]. Furthermore, the implementation of delivery observation using structured checklists and tools has been shown to increase adherence to essential birth practices and reduce severe complications [31]. By combining LDHF practice with ongoing supervisory checklists, we anticipate that this study will address the “know–do” gap often seen in maternal health programs.

### 3.5. Limitations

The protocol assessment will involve a pre–post design without a control group; therefore, the findings may be influenced by concurrent government programs, hospital maintenance issues, or external factors. Additionally, the reliability of the retrospective baseline data depends on the quality of the historical facility registers; however, this factor will be mitigated by a robust data cleaning and cross-verification process. The contribution of supplies and consumables, both to support the innovations and in addition to IPC and routine supplies, cannot be independently measured.

### 3.6. Sustainability and Policy Implications

Sustainability was incorporated into the protocol through an 18-month “Sustainability Phase” aimed at transitioning ownership to the MoHS. By utilizing a “train-the-trainer” model and integrating national trainers, the project will ensure that capacity will remain within the system after the implementation phase concludes.

## 4. Conclusions

This bundle of service delivery improvements represents a significant effort to operationalize national child and maternal survival priorities within a network of nine facilities. By combining high-impact training and technologies with a sustainable mentorship model, the aim of this bundle is to bridge the gap between policy intent and clinical reality, improving quality of care and reducing the burden of preventable deaths.

## Figures and Tables

**Figure 1 mps-09-00096-f001:**
[figure not shown]
Project alignment with national goals.

**Figure 2 mps-09-00096-f002:**
[figure not shown]
Implementation logic model.

**Table 1 mps-09-00096-t001:** Baseline characteristics and target training populations of participating healthcare facilities (2023).

Facility Name	Location (City)	Number of Annual Births	Maternal Deaths (2023)	Neonatal Deaths (2023)	Number of Annual C/S	Healthcare Workers Trained in Past 2 Years	Total Healthcare Workers to Be Trained
Bo Government Hospital	Bo	3226	34	191	1053	28	23
Jenner Wright Clinic	Freetown	412	17	6	14	13	-
King Harman Road Government Hospital	Freetown	712	8	15	331	9	87
Kissy CHC	Freetown	440	17	4	3	19	-
Princess Christian Maternity Hospital	Freetown	7099	63	464	3016	12	125
Rokupa Government Hospital	Freetown	1495	1	54	599	5	65
Ross Road CHC	Freetown	626	3	1	3	29	-
St. Anthony’s CHC	Freetown	511	19	2	5	27	-
Waterloo CHC	Waterloo	1015	17	11	20	8	23

**Table 2 mps-09-00096-t002:** Education and training.

Category	Indicator	Definition
Training uptake	Number of healthcare workers trained	Total number of midwives, nurses, physicians, and other staff completing WHO ENCC and PPH training modules
	Training completion against targets	Number completing training/facility training target
Skills retention	Frequency of LDHF practice sessions	Number of documented low-dose, high-frequency practice sessions per facility
	OSCE performance scores	Percentage of participants achieving competency on Objective Structured Clinical Examinations (OSCEs)
	Skills retention at 12 months	Percentage of trained staff maintaining competency at 12-month reassessment
Mentorship and supervision	Mentorship visits completed	Number of supportive supervision and mentorship visits conducted per facility
	Practice corner utilization	Frequency of use of facility-based LDHF practice stations

**Table 3 mps-09-00096-t003:** Maternal and newborn measures with definitions.

Category	Indicator	Definition
Maternal indicators	PPH incidence (500 cc)	[# of PPH incidence (500 cc)]/[total births]
	Uterotonics used for PPH prevention	[# of uterotonics used for PPH prevention]/[total births]
	Direct obstetric case fatalities	[# maternal deaths]/[# of total births]
	Admission triage scans	[# of ultrasound scans]/[# of maternal admissions]
	Abnormal scan findings	[# of abnormal scans]/[# of scans]
Neonatal indicators	Fresh stillbirths	[# of fresh stillbirths]/[total births]
	Neonatal case fatality rate < 24 h	[# of neonatal deaths < 24 h]/[total births]
	Neonatal case fatality rate < 48 h	[# of neonatal deaths < 48 h]/[total births]
	Neonatal transfers from maternity	[# of neonatal transfers from maternity]/[total births]
	Sick newborns on bCPAP	[# on bCPAP]/[# of SCBU admissions]
	Survival of sick newborns	[# survive SCBU admission]/[# of admissions]

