### 2.3. Implementation (The Service Delivery Bundle)

The service delivery bundle comprises a newborn package and a maternal package, supported by cross-cutting implementation strategies.

Newborn Care PackageCurriculum: Implementation of the World Health Organization Essential Newborn Care Course (ENCC) Parts 1 and 2.Respiratory Support: Training and deployment of Vayu bCPAP systems and Vayu oxygen blenders to prevent hyperoxic lung injury and retinopathy of prematurity.Equipment: Provision of bag-and-mask devices, suction units, heart rate monitors, and pulse oximeters, in addition to Vayu bCPAP systems, oxygen blenders, and consumables.Kangaroo Mother Care (KMC): Expansion of KMC, to ensure neonatal euthermia, for the immediate care of small and sick newborns.Maternal Care PackagePPH Management: Implementation of the WHO Postpartum Hemorrhage Package, including blood-loss quantification aids, intrauterine balloons, and anti-shock garments.Advanced Diagnostic Equipment: Training and deployment of Butterfly iQ3 handheld ultrasound probes (POCUS) for delivery wards and point-of-care hemoglobin testing.Risk Stratification: Enhanced triage and risk assessment using handheld ultrasound, improved use of fetal Dopplers and sphygmomanometers, and hemoglobin testing.Cross-cutting StrategiesRespectful Care: Principles and practices of respectful care will be integrated into clinical training and mentoring activities.Infection Control and Prevention (IPC) Supplies: Refresher training and supplies to improve water, sanitation, and hygiene practices.Service Optimization: Facility-based teams will identify unique challenges and implement and document improved practices.Implementation StrategyMentorship: Project HOPE will supply external mentors to cascade training and provide supportive supervision while observing patient care practices.Champions: Two internal “Champions” will be recruited at each facility to support training scale-up and practice.Practice Corners: Establishment of LDHF practice stations for skills retention.Ancillary Services, Equipment, and SuppliesData: Mentoring healthcare staff with documentation challenges and collecting and cleaning data.Equipment: Ancillary equipment includes Dopplers, stethoscopes, pulse oximeters, sphygmomanometers, thermometers, glucometers, oxygen concentrators, heart rate monitors, resuscitation equipment, and training simulators.Supplies: Consumables for bCPAP, hemoglobin, and urine testing, WASH equipment and supplies, personal protective equipment and sanitation supplies, hemorrhage kits and commodities, and printed materials.

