#### 2.4.2. Implementation Outcomes

Implementation success will be evaluated through metrics of fidelity, uptake, and sustainability:Fidelity and Adherence: The proportion of eligible SCBU admissions successfully initiated on Vayu bCPAP; the proportion of deliveries utilizing active management of the third stage of labor (AMTSL) with uterotonics; and the proportion of obstetric admissions receiving triage ultrasound scans.Uptake and Penetration: The total number of healthcare workers (midwives, nurses, physicians) successfully completing the WHO ENCC and PPH training modules against facility targets.Sustainability and Retention: The frequency of documented low-dose high-frequency (LDHF) practice sessions per facility; and objective skills retention measured via Objective Structured Clinical Examinations (OSCEs) at 12-month intervals.

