### 2.5. Outcome Measures

Outcome indicators, definitions, and data sources are summarized in Table 2. Primary outcomes are institutional maternal mortality, neonatal mortality within 24 h of birth, intrapartum stillbirth, and PPH incidence. Secondary outcomes include process indicators (e.g., uterotonic coverage for AMTSL, proportion of obstetric admissions receiving triage ultrasound) and intermediate clinical indicators (e.g., proportion of sick newborns initiated on bCPAP, SCBU survival).

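### Triage-ultrasound coverage is defined as a proportion of admissions, but the Table 3 formula divides scans by admissions, so it overstates coverage if any admission has a second or non-triage scan

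*Protocol article*

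**What the plan says.** Section 2.4.2 (Implementation Outcomes) lists three fidelity measures. One is "the proportion of obstetric admissions receiving triage ultrasound scans". Section 2.5 (Outcome Measures) repeats it among the secondary process indicators as the "proportion of obstetric admissions receiving triage ultrasound". In both places the unit is the admission.

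Table 3 (Maternal and newborn measures with definitions) has a row labelled "Admission triage scans". Its formula has the number of scans on top and the number of admissions below: "of ultrasound scans]/[# of maternal admissions". The numerator is not restricted to triage scans, and there is no rule that an admission counts once.

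Section 2.7 (Data Analysis) says that the indicators in Tables 2 and 3 are the ones to be compared between the baseline and final periods, so the Table 3 formula is the operative one. (Sections 2.5 and 2.6 appear to swap the two table numbers, but the scan formula is printed only in the clinical table.)

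**The concern.** A proportion of admissions and a number of scans per admission are different quantities. The first answers how many women were triaged with ultrasound. The second also rises when women already scanned are scanned again, or when a woman missed at triage is scanned later. Under the printed formula, rescanning some women can offset others who were never scanned, and the result would still be read as coverage.

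Later scans are possible under the plan, since Section 2.3 provides for "Training and deployment of Butterfly iQ3 handheld ultrasound probes (POCUS) for delivery wards". Section 3.2 names ultrasound in the maternity unit as one of two key innovations, and this row is the only coverage measure printed for it.

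There are two practical consequences. Section 2.7 lists chi-square among its methods, and a ratio that can exceed 1 is not a binomial proportion to which that test applies. Section 2.8 says that extracted data will be aggregated by facility. If scan totals are what is aggregated, the number of admissions scanned cannot be recovered afterwards.

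**Working it through.** The article states no expected scan count, repeat-scan rate or coverage target for this indicator, so there is no figure of its own to reproduce. The check is an identity from the two definitions, followed by illustrations on assumed values. Obstetric admissions (text) and maternal admissions (table) are taken to be the same denominator.

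**Identity.** Let N be admissions, T the admissions with at least one triage scan, and S all scans.

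- Outcome in Sections 2.4.2 and 2.5: T/N.
- Table 3 value: S/N.
- S = T + (further triage scans in the same admissions) + (scans outside triage).
- So S/N − T/N = (further triage scans + scans outside triage)/N. This is never negative. It is zero only when each scanned admission has exactly one scan and that scan is at triage.

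**A three-admission example.** Woman A has a triage scan and two later repeats, woman B has no scan, and woman C has only a later scan in labor.

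- Defined outcome: 1/3 = 33%.
- Table 3 read literally: (3 + 0 + 1)/3 = 4/3 = 133%.
- Table 3 with the row label limiting the count to triage scans: 1/3 = 33%, which agrees. If one of A's repeats is instead done during triage, the label-limited count is 2/3 = 67%, and the defined outcome is still 33%.

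**Size on assumed values.** Suppose every scanned admission was scanned at triage. Write c for true coverage and m for mean counted scans per scanned admission. Then the Table 3 value is c × m, and it passes 100% when m > 1/c.

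| True coverage c | m = 1.0 | m = 1.1 | m = 1.2 | m = 1.3 | m = 1.5 | Passes 100% above m = |
|---|---|---|---|---|---|---|
| 50% | 50% | 55% | 60% | 65% | 75% | 1/0.5 = 2.00 |
| 70% | 70% | 77% | 84% | 91% | 105% | 1/0.7 = 1.43 |
| 80% | 80% | 88% | 96% | 104% | 120% | 1/0.8 = 1.25 |
| 90% | 90% | 99% | 108% | 117% | 135% | 1/0.9 = 1.11 |

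The relative overstatement is m − 1 whatever the coverage: none at m = 1.0 and 30% at m = 1.3.

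The value also cannot be inverted without m. A reported 75% fits true coverage of 75% (0.75 × 1.0), 60% (0.60 × 1.25) or 50% (0.50 × 1.5).

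**After the correction.** With admissions scanned at triage as the numerator, the indicator is c in every cell and cannot exceed 100%.

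**The case against.** The strongest reply is that Table 3 is written in shorthand and its formulas lean on their labels. Read with "Admission triage scans", the numerator is triage scans, probably close to one per admission, and the table then nearly agrees with the text, which fixes the admission as the unit twice. Counting rules can also be left to a fuller document. Part of this stands: the label may exclude later scans, and with one triage scan per admission the two definitions coincide. But the label does not stop two triage scans in one admission from counting twice. Nor is this a detail left unsaid, because a formula is printed and it differs from the outcome it is meant to measure.

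It is also fair that the size is entirely assumed, that Section 2.5 classes this as a secondary process indicator, and that Section 1.4 sets no numeric target for ultrasound.

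A reader might infer that the next row, abnormal findings, is inflated in the same way. The documents do not support that. The row is "of abnormal scans]/[# of scans", with the scan as the unit above and below, and no section defines it per woman. If first scans are abnormal with rate p, and there are e extra scans per scanned admission that are abnormal with rate q, the per-scan rate is (p + e × q)/(1 + e), which exceeds p only if q > p. With assumed p = 15% and e = 0.2:

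- q = 5%: 0.16/1.2 = 13.3%
- q = 15%: 0.18/1.2 = 15.0%
- q = 50%: 0.25/1.2 = 20.8%

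Repeats can therefore lower the rate, leave it unchanged or raise it.

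A reader might also expect more inflation at hospitals than at community health centers. The article says nothing about rescanning by type of facility.

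**Conclusion.** The point holds for the coverage row. The text and Table 3 define different quantities under one name, and the printed formula can only equal or overstate the coverage that the text describes. That direction follows from the definitions and needs no assumption beyond a common denominator.

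The amount is unknown. It depends on scans per scanned admission and on whether scans outside triage are counted, and the article gives neither. The overstatement may be nil; values above 100% need, for example, more than 1.25 counted scans per scanned admission at 80% true coverage.

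The consequence is limited to a secondary fidelity indicator. No primary outcome or effectiveness conclusion depends on it, and the abnormal-findings row is a coherent per-scan rate.

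**What to change.** In Table 3, set the numerator of the triage-scan row to the number of maternal admissions with at least one ultrasound scan at admission triage, each admission counted once, over the number of maternal admissions. If total scanning activity is of interest, report scans per admission on a separate line as workload, not as coverage. The abnormal-findings row need not change.

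The cost is one changed numerator, plus extraction that counts admissions scanned rather than scans. Where registers hold only scan totals, that means recording whether each admission had a triage scan, so the rule should be settled before facility totals are compiled. Reported coverage will be equal to or lower than under the present formula.

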Meanwhile, the maternal mortality rate (MMR) in Sierra Leone remains unacceptably high at 443 per 100,000 live births, placing it among the worst 15 countries worldwide [2,3,17]. Postpartum hemorrhage (PPH) is the leading global cause of maternal mortality and is particularly deadly in resource-constrained settings, where detection and treatment can be delayed [3].

Intrapartum complications, such as hemorrhage, labor dystocia, fever, abnormal lie, and fetal distress, may lead to perinatal asphyxia, worsening outcomes for both the mother and baby [18,19,20,21,22]. To mitigate these risks, the integration of obstetric ultrasound in LMIC maternity units has proven highly valuable [23]. Evidence indicates that routine ultrasound use significantly improves diagnostic accuracy and risk stratification for high-risk conditions, such as placenta previa, malpresentation, and multiple gestations, enabling timely referrals and appropriate clinical management before emergencies arise [23]. Thus, more effective recognition and treatment of hemorrhage, combined with enhanced maternal risk assessment and case management, can improve maternal outcomes.

The aim of this protocol is to describe a targeted newborn and maternal bundle that will be implemented in Sierra Leone, as shown in Figure 1. The newborn bundle combines improving and sustaining high-quality neonatal resuscitation with utilization of bCPAP for respiratory distress treatment. The maternal bundle combines improved intrapartum risk assessment with high-quality prevention and treatment of maternal hemorrhage.

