### 1.4. Objectives

The primary objective of implementing a targeted service delivery bundle is to enhance maternal and newborn outcomes in a cohort of nine hospitals over a three-year period. These service delivery improvements aim to achieve the following:Reduce neonatal mortality: Achieve a 50% reduction in neonatal deaths within the first 24 h and a 10% reduction in intrapartum or “fresh” stillbirths compared to a baseline assessment.Reduce neonatal morbidity: Achieve a 25% reduction in neonatal transfers to advanced care.Improve neonatal clinical practice: Ensure that 80% of SCBU admissions with respiratory distress receive appropriate oxygen therapy.Reduce maternal morbidity: Achieve a 40% reduction in the incidence of postpartum hemorrhage and a 50% reduction in institutional maternal mortality.Improve obstetric clinical practice: Ensure that 90% of deliveries utilize active management of the third stage of labor with uterotonics to prevent hemorrhage.Strengthening diagnostic capacity: Deploy handheld ultrasound and point-of-care hemoglobin testing to improve obstetric risk stratification.Maintain competency: Implement a “train-the-trainer” model, mentoring, low-dose high-frequency practice, and supportive supervision to maintain high performance on knowledge and skills checks at 12-month intervals.

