### 2.2. Setting and Geographic Clusters

The bundle implementation will be conducted in nine public health facilities in Sierra Leone: eight in the Greater Freetown area and one in the city of Bo, including one tertiary hospital, four secondary hospitals, and four community health centers (CHCs), as described below and in Table 1.

Participating facilities:Tertiary: Princess Christian Maternity Hospital (PCMH)—Freetown.Secondary: Bo Government Hospital, Rokupa Government Hospital, King Harman Road Government Hospital, and Waterloo CHC (functioning as a secondary hospital).Primary (CHCs): Jenner Wright, Kissy, Ross Road, St. Anthony’s (Note: These CHCs do not perform cesarean sections or care for small/sick newborns.).

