### 2.6. Data Collection

Data collection is stratified by outcome type:Clinical Data (See Table 2): Quantitative will be collected from existing Ministry of Health (DHIS2) systems and project-specific sources. Project data collectors will collaborate with medical record officers to extract granular clinical data from consecutive maternity and newborn registers across all nine facilities. A preliminary review for validation and missing entries will be followed by cross-verification. Outcomes observed during the implementation and sustainability periods will be compared with retrospective baseline data collected three months prior to training.Implementation and Educational Data (See Table 3): Quantitative implementation metrics, including training logs and low-dose high-frequency (LDHF) practice frequencies, will be extracted from facility-level project registers. Educational indicators, such as performance on objective structured clinical examinations (OSCEs) and skills retention at 12 months, will be collected and tabulated by the mentorship teams.Qualitative data: Qualitative insights regarding implementation barriers and skill retention will be obtained from selected facility staff interviews, debriefs, and surveys.

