### 2.8. Ethical Considerations

Because this protocol is structured as a service delivery program review rather than a clinical trial, it does not involve human subjects research. All clinical elements of the newborn and maternal packages are standard, evidence-based practices with ample prior evidence of benefits and minimal risk of harm. The assessment relies exclusively on the secondary analysis of routine programmatic data and information mandated by the Ministry of Health and Sanitation (MoHS). All extracted clinical data will be fully anonymized and aggregated at the facility level, ensuring the de-identification of patient outcomes. Prior to implementation, the project was carefully evaluated by the MoHS and approved.

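### Table 3 does not limit the 24 h and 48 h neonatal death rates to babies born in the nine facilities, so the rates can move with referral across the network boundary

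*Protocol article*

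**What the plan says.** The clinical formulas stand in Table 3. The 24 h neonatal indicator is the number "of neonatal deaths < 24 h]/[total births"; the 48 h indicator has the same form. The maternal indicator is the number of "maternal deaths]/[# of total births". No entry says whether the baby must have been born, or the woman delivered, in a participating facility, or where a death after transfer is counted.

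Neonatal death within 24 h is primary in section 2.4.1 and again in section 2.5: "Primary outcomes are institutional maternal mortality, neonatal mortality within 24 h of birth, intrapartum stillbirth, and PPH incidence". The maternal death indicator is primary in section 2.5 but secondary in section 2.4.1.

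Under section 2.6, project staff will "extract granular clinical data from consecutive maternity and newborn registers across all nine facilities". Section 2.8 adds: "All extracted clinical data will be fully anonymized and aggregated at the facility level".

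On patient movement, section 2.2 says of four of the nine sites: "These CHCs do not perform cesarean sections or care for small/sick newborns". Section 1.4 sets the aim: "Achieve a 25% reduction in neonatal transfers to advanced care". The limitations in section 3.5 do not mention referral.

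The level of analysis is not fixed. Section 1.4 speaks of a cohort of nine hospitals, section 2.1 appeals to comparisons within facilities, and section 2.7 lists paired and unpaired tests without naming the unit.

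**The concern.** A death rate per birth describes risk only if the deaths come from the births in the denominator. Newborn registers at a hospital with a special care unit can hold babies born elsewhere, and a facility's records need not show the fate of a baby sent away. Read literally, the Table 3 formula counts the former as deaths and loses the latter.

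A mismatch that stayed constant over three years would matter less. Here the comparison is between three months before the project and its last three months, and the project sets out to change transfers and to expand newborn respiratory care. If flows into or out of the network change between those windows, the primary rate changes with them. The reader could not then tell a change in risk among babies born under the bundle from a change in who was transferred.

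**Working it through.** **1. Which cases mismatch under the literal formula**

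| Born | Died within 24 h | Birth counted | Death counted | Consequence |
|---|---|---|---|---|
| Network site | Same site | yes | yes | matched |
| Network site | Another network site | yes | yes | matched if pooled; mismatched by facility |
| Outside network | Project newborn unit | no | yes | death without a birth |
| Network site | Outside network | yes | no | birth without a death |
| Network site, mother referred in before delivery | Network site | yes | yes | matched; case mix changes |

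Only the third and fourth rows affect a pooled rate.

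**2. What Table 1 shows (2023, all neonatal deaths)**

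The article gives no baseline for deaths under 24 h, so there is no stated figure to reproduce. Deaths per 1000 births from Table 1:

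- Four community health centers (CHCs): (6+4+1+2)/(412+440+626+511) = 13/1,989 = 6.5
- Tertiary hospital: 464/7,099 = 65.4
- Bo: 191/3,226 = 59.2
- All nine: 748/15,536 = 48.1

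Referral would give this gradient, but so would case mix. The table cannot separate them.

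**3. Sensitivity to inward referral (assumed inputs)**

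Let s be the share of counted deaths born outside the network and c the relative change in those deaths as inward referral changes, with inborn risk and births held fixed. The new rate is the old rate × [(1 − s) + s(1 + c)], so the relative change is s × c.

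| s (assumed) | c = ±25% | c = ±50% | Inborn-only rate, 48.1 × (1 − s) |
|---|---|---|---|
| 10% | ±2.5% | ±5% | 43.3 |
| 20% | ±5% | ±10% | 38.5 |
| 30% | ±7.5% | ±15% | 33.7 |
| 50% | ±12.5% | ±25% | 24.1 |

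The inborn-only rate (per 1000) does not depend on c.

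**4. Dilution of the target**

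Section 1.4 aims at a 50% fall in deaths within 24 h. If inborn deaths halved and outborn deaths did not change, the observed fall would be 50% × (1 − s): 45%, 40%, 35% and 25% for s = 10%, 20%, 30% and 50%.

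**5. Transfers inside the network**

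Suppose 30 of the tertiary hospital's deaths were babies born at the CHCs (assumption). By facility of birth, the tertiary rate becomes (464 − 30)/7,099 = 61.1 instead of 65.4, and the CHC rate (13 + 30)/1,989 = 21.6 instead of 6.5. The pooled rate stays at 748/15,536 = 48.1.

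**6. Maternal deaths**

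CHCs: 56/1,989 = 28.2 per 1000 births. Other five sites: 123/13,547 = 9.1 per 1000. This runs opposite to what loss of deaths through referral out would produce.

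**The case against.** The strongest reply is that Table 3 holds one-line formulas in a condensed article and nowhere says that outborn deaths are counted; an inborn rule may sit in the full protocol. That is fair for operational detail. But Table 3 is offered as the definitions, and for a primary outcome drawn from newborn registers the population of the numerator belongs in the definition.

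Other points limit the concern, and they stand:

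- A reader might infer that each facility's deaths are divided by its own births, so that the CHCs look better and the receiving hospitals worse. Table 3 names no level. That distortion arises only if facility-level rates are compared.
- A reader might take the Table 1 gradient as proof of displacement. It covers all neonatal deaths and may be case mix. For the 24 h rate, an outborn baby must be born elsewhere, transferred and dead within one day, so the outborn share may be smaller; nothing in the article gives it.
- Section 1.1 describes obstetric ultrasound as "enabling timely referrals and appropriate clinical management before emergencies arise". A woman referred before delivery brings her birth with her, so this alters case mix rather than producing a death without a birth.
- The article nowhere says that better newborn units will attract outside referrals. The transfers targeted for reduction may also include moves from maternity to special care in the same hospital, which leave the ratio unchanged.
- A reader might extend the point to mothers generally. The maternal figures in Table 1 do not show deaths vanishing through referral.
- Aggregation does not by itself rule out correct attribution, because section 2.6 plans detailed extraction from the registers.
- Table 3 already has a survival indicator over special care admissions, and outborn babies treated there also receive the bundle. Their improved survival can be a real effect, but it belongs over their own denominator.

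**Conclusion.** The concern holds for the 24 h (primary) and 48 h neonatal death rates at the network boundary: numerator and denominator need not describe the same babies, and a before-after change in referral can pass for a change in risk. The direction is not fixed. More outborn admissions, or fewer inborn babies sent outside the network, would raise the observed rate; the reverse would lower it.

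The size is unknown. The illustrative movement of 2.5% to 12.5% rests on an assumed outborn share of 10% to 50%, an assumed 25% change in inward referral with deaths changing in proportion, and constant inborn risk. Within the network, the problem exists only if rates are compared by facility, which sections 2.1, 2.7 and 2.8 leave open. For maternal deaths it is confined to women referred in after delivery or dying undelivered.

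**What to change.** Before the final-period data are extracted, amend Table 3 as follows and apply it identically in both periods:

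1. Restrict the numerator of the 24 h and 48 h rates to babies born in one of the nine facilities, using an inborn/outborn mark made at register extraction, before aggregation.
2. Tabulate outborn deaths separately, over outborn admissions.
3. Report the number U of inborn babies transferred outside the network as outcome unknown. With D known inborn deaths and B births, give the bounds D/B (all alive) and (D + U)/B (all dead).
4. State whether rates are pooled or compared by facility. If by facility, attribute each death to the facility of birth where the registers record it; otherwise rely on the pooled rate.
5. Tabulate maternal deaths among women referred in after delivery, or dying undelivered, separately from those among women delivered in a project facility.

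The cost is one extra field in an extraction already planned and revised formulas. Attribution by facility of birth costs more, since the receiving site must have recorded the specific facility. Baseline registers may lack place of birth for some babies; they go into an unknown row, and the rate can be shown with that row counted as inborn and as outborn.
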